##### Suspected unexpected serious adverse reaction

AE that are serious or are important medical events, that are judged to be related to study product administration, and that are unexpected based on the information contained in the reference safety information will be termed suspected unexpected serious adverse reactions (SUSARs)

#### Solicited adverse events

The following solicited local and systemic adverse events will be collected and graded for severity based on the National Institute of Health (NIH), Division of AIDS (DAIDS) Table for Grading the Severity of Adult and Pediatric adverse events (version 2.1. Jul 2017):Adult local: pain, redness/erythema, swelling/induration, pruritisToddler and infant local: pain, redness/erythema, swelling/indurationAdult systemic: acute allergic reactions (day 0 only), axillary temperature, vomiting, diarrhoea, headache, fatigue, myalgia, arthralgia and rashToddler and infant systemic: acute allergic reactions (day 0 only), axillary temperature, vomiting, diarrhoea, irritability, drowsiness, appetite and rash

Solicited AE will be recorded on the day of study product administration (visit 1 — day 0) by the study clinician and daily through home visits conducted by trained field workers between day 1 and day 13 post-study product administration. Any local and systemic AE ongoing after day 13 will be recorded by the study clinician as an unsolicited AE at the day 14 clinic visit (visit 3). Any grade 3 solicited AE identified during home visits will prompt an unscheduled clinic visit and review by a clinical study clinician on the same day or within 24 h at the latest.

Solicited AE data from home visits will be reviewed daily by a study clinician. In addition, home visits will be spot checked by senior members of the field team to ensure the quality and consistency of findings.

#### Unsolicited adverse events

Any event fulfilling the definition of an AE, but which is not reported based on the definition of solicited local and systemic AE will be reported as unsolicited AE. When possible, collections of individual signs and symptoms will be reported as the underlying clinical syndrome. For example, gastroenteritis should be reported rather than diarrhoea, vomiting and fever. If an underlying clinical syndrome is not apparent, symptoms and signs will be reported individually. Unsolicited AE will be coded by preferred term (PT) and primary system, order, class (SOC) for reporting according to the latest online version of the MedDRA®.

#### Classification of adverse events

##### Severity

Solicited local and systemic AE as well as unsolicited AE will be graded for severity based on the NIH DAIDS Table for Grading the Severity of Adult and Pediatric AE (version 2.1. Jul 2017) or, if not included, based on the criteria set out in Table 5. The highest severity grade applicable at any point during an illness will ultimately be reported. Any AE which results in death will be defined as severity grade 5.

**Table 5 Tab5:** Severity grading for unsolicited adverse events^a^

		Description
Grade 1	Mild	No interference with activity and no or minimal intervention^1^ required
Grade 2	Moderate	Some interference with activity or requires more than minimal intervention
Grade 3	Severe	Prevents daily activity and required significant medical intervention
Grade 4	Life-threatening	Life-threatening consequences requiring urgent medical intervention
Grade 5	Death	Results in death

^a^Adapted from Cancer Therapy Evaluation Program, Common Terminology Criteria for AEs, version 3.0, DCTD, NCI, NIH, DHHS March 31, 2003, published on August 9, 2006

^1^One or two doses of antipyretic or simple analgesic medication or local topical treatment

##### Causality

Other than solicited local reactions which, by definition, are related to study product administration, other AEs will be assessed for relatedness to the study vaccine by a study clinician.

The relatedness of a particular AE will be assessed based on clinical judgment considering the timing of the event in relation to study product administration, the nature of the event, the presence or absence of other illnesses or conditions to explain the event and relevant background history and concomitant medication use.

Based on these assessments, the relationship between a given AE and study product will be defined as:Related^2^: There is a reasonable possibility of a causal relationship between the AE and the study product administered. The AE is more likely to be explained by the administration of the study product than by another cause.Not related: There is not a reasonable possibility of a causal relationship between the AE and the study product administered. The AE is more likely to be explained by another cause.

Given the double-dummy design, at the time of the initial unblinded assessment of an AE, it will not be possible to establish whether systemic AE is related to the MRV-MNP or MRV-SC.

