### Outcomes {12}

#### Study outcome measures

#### Primary — safety and tolerability

The number, severity and relatedness of solicited local and systemic AEs collected on the day of study product administration and daily until day 13 following study product administrationThe number, severity and relatedness of unsolicited AE and SAE from the day of study product administration until day 180 following study product administrationThe number, severity and relatedness of biochemical and haematological abnormalities occurring until day 14 (adult cohort only) or day 7 (toddler and infant cohorts) following study product administration

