### Participant timeline {13}

The participant timeline is shown in Table 1.

**Table 1 Tab1:** Participant timeline

Visit #	V0	V1	Home visits	V2	V3	V4	V5
Study day	−14 to −1	0	1 to 13	7	14	42	180
Visit window (days)	-	-	-	+2	+3	+14	+28
Written informed consent	X						
History and physical examination	X	X		X	X	X	X
Vital signs and anthropometry	X	X		X	X	X	X
Screening and safety labs	X			X	X^a^		
Serum pregnancy test^b^	X						
Urinary pregnancy test^b^		X					X
Malaria rapid diagnostic test/blood film	X	X					
Immunogenicity blood samples	X					X	X
Final confirmation of eligibility		X					
Randomization and study product administration		X					
Solicited local and systemic AE data collection		X	X	X	X		
Unsolicited AE collection		X	X	X	X	X	X
EPI vaccine administration^c^						X	
T-cell responses — exploratory	X			X		X	X
Participant/parent experience — exploratory		X X^d^			X	X	
End of study							X‖

^a^Adult cohort only; ^b^adult females only; ^c^toddlers and infants will be administered the other EPI vaccines due at 15 to 18 months and 9 to 10 months/12 months respectively at V4 (day 42);^d^pre-vaccination (may also be conducted at V0) and post-vaccination; ‖toddlers and infants will be administered an additional SC dose of a measles and rubella vaccine on or after the end of study visit outside the current protocol to ensure protection based on the current EPI schedule in The Gambia

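### Related and Not related each carry two different causality thresholds, so an adverse event with a plausible but less likely vaccine cause has no determinate class

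*Protocol article*

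**What the plan says.** The protocol article's Outcomes section makes relatedness part of the primary outcome. For solicited events it is "The number, severity and relatedness of solicited local and systemic AEs collected on the day of study product administration and daily until day 13", with parallel items for unsolicited AEs and SAEs to day 180 and for laboratory abnormalities.

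The Causality section treats solicited local reactions as related by definition. A study clinician judges every other AE, weighing timing, the nature of the event, other explanations, history and concomitant medication. The result must be one of two classes, and each is defined by two sentences:

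- Related: causation by the study product is reasonably possible; and "The AE is more likely to be explained by the administration of the study product than by another cause".
- Not related: causation is not reasonably possible; and "The AE is more likely to be explained by another cause".

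On the secondary point, the section on solicited adverse events states: "Any local and systemic AE ongoing after day 13 will be recorded by the study clinician as an unsolicited AE". The section on unsolicited adverse events covers any event that meets the AE definition "but which is not reported based on the definition of solicited local and systemic AE will be reported as unsolicited AE".

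**The concern.** The first sentence in each pair sets a possibility bar and the second sets a comparative bar. These are different questions. A cause can be reasonably possible without being the most likely one, and the section does not say which sentence governs or how the two combine. The AEs caught between the bars are those for which a relatedness rule is most needed.

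Such cases are foreseeable. The protocol's account of known potential risks lists mild fever and rash as vaccine reactions. Temperature and rash are solicited systemic terms in toddlers and infants, and a fever during an intercurrent infection is an obvious example. The study clinician makes the call when the event occurs, so an analysis rule written later cannot fully repair it.

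**Working it through.** There is no plan figure to reproduce; this is a check of logic. Describe an AE by two facts: whether vaccine causation is reasonably possible, and which cause is likelier. Apply the Causality wording first with both sentences required, then with either sentence enough.

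| Reasonably possible? | Likelier cause | Both sentences required | Either sentence enough |
|---|---|---|---|
| Yes | Product | Related | Related |
| Yes | Other | Neither class | Both classes |
| Yes | Equal | Neither class | Related |
| No | Product | Neither class | Both classes |
| No | Other | Not related | Not related |
| No | Equal | Neither class | Not related |

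The fourth row is not a realistic combination, and the sixth is hardly one. The second row is realistic and is the problem: no single class results under either way of joining the sentences. If one sentence is taken to govern alone, the answer depends on which:

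- Possibility sentence governs: the second-row AE is Related.
- Likelier-cause sentence governs: the same AE is Not related, and ties remain open.

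The class then feeds four places in the protocol:

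1. **Primary outcome.** Relatedness is tabulated for solicited, unsolicited and laboratory events.
2. **SUSAR definition.** The event must be judged related.
3. **Expectedness.** The sponsor's medical expert assesses it for related unsolicited AEs only. An unsolicited AE classed Not related receives no expectedness review and cannot become a SUSAR.
4. **Pause criteria (Interim analyses).** Four of the five depend on relatedness: any SUSAR, related death, related systemic or laboratory events above grade 3, and the 20% rule for the same related event above grade 2. Only the criterion for solicited local events does not use a relatedness judgement.

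The 20% rule shows how one judgement can matter. Suppose, for illustration, that all 45 adults have been dosed. The threshold is 0.20 × 45 = 9 participants. If nine have the same event and one is a second-row case, the count is 9/45 = 20.0% when that case is Related and 8/45 = 17.8% when it is Not related. The criterion is met in the first case and missed in the second.

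Secondary check. Solicited events are counted to day 13 and unsolicited events to day 180. A continuous event recorded as solicited and then, after day 13, as unsolicited can enter both counts, although the unsolicited class is described as holding events not reported as solicited. The protocol also does not say whether a local reaction keeps its related-by-definition status once it carries the unsolicited label.

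**The case against.** The strongest reply is that the second sentence explains the first: Related means that the product is the likelier explanation, and Not related means that something else is. The classes then do not overlap and only ties are open. This reading is available, but the text does not impose it. It also leaves the possibility sentences with no work to do, and a clinician could as readily treat those as the test. The footnote attached to Related is not shown and may clarify the intent. Its absence is not a fault in the plan, but the two visible sentences would still need reconciling. Reliance on clinical judgement is proper, but judgement needs one question to answer.

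A reader might also infer more than the documents support:

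- **That the errors favour the patch.** Every participant receives a patch and an injection, and those assessing endpoints are blinded, so any threshold applies alike to both arms. The Causality section does call the initial assessment unblinded. However, the same sentence says that the source of a systemic event cannot be told, so blinded is evidently meant.
- **That Table 5 contradicts itself.** Grade 3, "Prevents daily activity and required significant medical intervention", joins two conditions where grade 2 offers alternatives. It can be read coherently, with grade 3 needing both conditions and lesser combinations falling to grade 2. Table 5 is a fallback for events not in DAIDS. The grade-based pause criteria concern solicited events, graded on DAIDS, and laboratory results, graded on a local scale.
- **That Table 1 conflicts with the day 13 limit.** The row "Solicited local and systemic AE data collection" is marked at visit 3 (day 14), which fits the clinician recording ongoing events at that visit.
- **That primary results are certainly double counted.** The carry-over rule is explicit, no summed total is specified, and the statistical analysis plan may settle tabulation. The proportion of participants with any AE would not change. This part is therefore secondary.

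**Conclusion.** The concern holds for the relatedness definitions. As visibly worded, an AE with a reasonable possibility of vaccine causation and a likelier alternative has no determinate class. If clinicians follow the likelier-cause sentence, such events leave Related, and the SUSAR route and the relatedness-dependent pause criteria become less sensitive in the first human use of this product. If they follow the possibility sentence, that loss does not arise, but the protocol does not tell them to.

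The effect is on absolute counts of related events and on safety triggers. There is no ground to expect bias between arms, provided that assessment is blinded as the design states. The number of AEs affected cannot be computed: the protocol gives no rate of borderline events and no probability scale for either bar. The conclusion also assumes that the unseen footnote does not already state which sentence governs.

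The carry-over of solicited events past day 13 is a lesser matter of consistency between two definitions.

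**What to change.** Reconcile the two sentences in each class so that one threshold separates Related from Not related and every AE falls in exactly one class. One way is to keep the possibility sentences alone and delete the likelier-cause sentences. The sponsor and investigator should choose the threshold and state it once. Carry the wording into the case report form guidance.

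The article reports recruitment as ongoing, so record the date of the change and have earlier borderline AEs re-reviewed blind to allocation under the same threshold. Otherwise counts could differ within or between cohorts because of the wording alone.

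As a secondary change, align the solicited and unsolicited definitions. A solicited AE that continues past day 13 should be linked to its solicited record and counted once, and a local reaction should keep its related-by-definition status.

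The cost is a wording amendment, brief retraining and the re-review. The number of related AEs may rise slightly.

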##### Expectedness

Expectedness, either ‘expected’ or ‘unexpected’, will be assessed for unsolicited related AE by the sponsor’s medical expert based on the latest Investigator’s Brochure for the MRV-MNP and summary of product characteristics (SmPC) for the SC injection. For systemic events, the SmPC will serve as the reference safety information for the purposes of assessing expectedness of any reactions to the MRV irrespective of administration methods. Therefore, any systemic reaction judged to be expected based on the SmPC for the MRV will also be defined as expected following MRV-MNP.

**Outcome**

The outcome of AE will be defined as resolved/recovered, resolved/recovered with sequelae, ongoing stable chronic condition, ongoing at end of the study visit, resulted in death and unknown.

##### Safety laboratory investigations

Screening (visit 0) and safety (visit 2 and visit 3 [adults only]) laboratory investigations will be performed in the MRCG CSD laboratories according to their Standard Operating Procedures (SOPs). The SOPs govern the processes of sample reception, sample processing and result reporting. The CSD biochemistry, haematology, microbiology and serology laboratories are all ISO15189 accredited and Good Clinical Laboratory Practice (GCLP) compliant.

All abnormal safety labs will be graded based on a locally appropriate grading scale and will be judged for clinical significance and relatedness. Abnormal safety labs will be repeated as clinically indicated.

##### Immunogenicity

Serum samples for measles and rubella serological testing will be shipped to the Centers for Disease Control and Prevention, National Center for Immunization and Respiratory Diseases, Division of Viral Diseases) for processing according to CDC SOP and Quality Control (QC)/Quality Assurance (QA) procedures.

Measles-specific SNA titres will be measured using the PRNT. A standardized PRNT protocol as recommended by the WHO will be used as previously reported [67, 68].

Rubella-specific SNA titres will be measured using the ICA as previously reported [69].

Measles and rubella-specific IgG concentrations will be measured using a multiplex bead array (MBA) assay established at the CDC [70].

Both the measles and rubella SNA titres and the measles and rubella IgG concentrations will be calibrated to the appropriate WHO standards to facilitate comparisons. The reference standard for measles will be WHO/BS/06.2031 (WHO International Standard, 3rd International Standard for Anti-Measles) and for rubella will be RUBI-1-94 (WHO International Standard; Anti Rubella Immunoglobulin, Human) [71, 72].

Measles seropositivity will be defined as a standardized titre of > 120mIU/mL.

Rubella seropositivity will be defined as a standardized titre of > 10IU/mL.

### Plans to promote participant retention and complete follow-up {18b}

During sensitization and informed consent procedures, the commitment that the trial involves will be emphasized to ensure participants/parents of participants do not join the trial unless they feel that they will be able to attend for the required visits and make time for the required home visits. Blood sample bottles containing a local juice (Wonjo) which has the appearance of blood are used to illustrate the blood volumes required given that this can be sensitive. At all planned visits, the participants/parents of participants will be reminded of the need to contact the study team both if they have any concerns about their/their child’s well-being and if they have any unexpected travel plans.

In addition, to facilitate communication, a telephone on a CUG network with all members of the field team will be provided to participants/parents to ensure they are able to contact the investigator team at any time day or night without the need for telephone credit.

Irrespective of the reason for withdrawal or discontinuation of a participant, the investigator should make every reasonable effort to ensure the safety of the participant. This includes — in order of general priority, continuing to:Assess and provide the clinical care for AE that would have occurred had the participant remained in the study or to ensure such assessment and care is available to the participantUndertake the safety follow-up planned in the study including the planned safety bloodsCapture planned safety data in the clinical trial database

### Data management {19}

All data management activities will be described in the Data Management Plan for the trial.

#### Data collection

Data collection in the field will be undertaken by members of the investigator team who are responsible for ensuring its accuracy, completeness, legibility and timeliness. Data required to assess non-laboratory-based trial endpoints will be collected onto electronic case report forms (eCRF). A source document designation log will define the source for all information to be collected. Some information will be collected directly into an eCRF based on the participant report; thus, the eCRF will be the source in this case. Additional source documents include other trial-specific documents (vital signs and anthropometry cards; sample collection logs; study product administration logs; study product accountability and cold-chain documentation; randomization documents; screening and enrolment log; trial clinical progress notes etc.) as well as non-trial-related documents (clinical records from any hospital/clinic admissions, printouts of clinical laboratory results and prescription charts, etc.).

Serological data from external laboratories will be received by MRCG electronically in a secure format and integrated with data in the clinical trial database for analysis. An original set of all external laboratory data received will be retained for future monitoring and audit purposes.

#### Clinical trial database

Trial data will be collected through eCRF into a clinical data management system (CDMS) designed within a 21 CFR Part 11 compliant with the REDCap™ platform. The platform allows data to be captured online but also offline. This is important given internet connectivity may be unreliable, particularly when data are being collected in the field through home visits.

The trial database will be developed by the database developer in liaison with the trial data manager as per the MRCG data management SOP on Database Development. Database validation will be documented prior to release

#### Data validation and cleaning

Data validation will be undertaken to identify missing, erroneous, implausible and inconsistent data and to identify protocol deviations — for example related to participant eligibility or visit windows. A combination of on-entry and batch validation will be used. All validations and procedures involved in data cleaning, performed manually or automatically by validation check programming, will be defined in the data management plan. Data queries will be raised real time based on the defined error checks for review and resolution by the investigator team through a defined change process maintaining a clear audit trail.

#### Data coding

All AE data will be coded by PT and primary SOC according to the latest online version of MedDRA®. Generic rather than brand names will be used for all concomitant medication.

#### Data security and storage

All data will be stored on access-controlled computers and servers in line with applicable MRCG data management and data security policies. Databases will be backed-up as part of MRCG information technology disaster recovery policy.

### Confidentiality {27}

All clinical trial data and samples will be collected and stored in a linked-anonymized format using the participant’s screening number. No participant identifiable information, or collection of data which would otherwise allow a participant to be identified by those outside the investigator team, will be stored in either the clinical trial database or with the trial samples.

Participant identifiable information (name, address, contact telephone numbers etc.) and information linking the screening and randomization numbers to the participant identifiable information will only be available to the investigator team collecting and storing the data. Such information will be stored in locked filing cabinets or other lockable storage devices at the clinical trial sites and will only be accessible to those members of the investigator team requiring such information for day-to-day trial conduct. The information will also be held in a secure, access restricted database which will be used to track participants and facilitate visit planning. This database is unrelated to the main clinical trial database and will only be accessible to those members of the investigator team requiring access for study coordination.

Clinical research associates and external auditors conducting on-site monitoring or audit would necessarily be given access to participant identifiable information to complete their work (e.g. to confirm the completeness of the participant identification code list or the accuracy of ICD completion). Information regarding who will have access to such data and confirming the purpose of such access will be included in the ICD. No participant identifiable data will be made available to other parties or laboratories involved in the trial or to other external researchers.

